#### b) Research Questions for this Study (in Lay language)

Can high precision radiotherapy suppress the function of the collection of nerves that cause dangerous heart rhythms?

Does this form of high precision radiotherapy have a favourable safety profile compared to alternative treatments (e.g. medications, cardiac ablation or surgical removal)?

Does high precision radiotherapy affect levels of circulating markers in blood samples known to increase risk of dangerous heart rhythms?

Does high precision radiotherapy result in a reduction in abnormal heart rhythms and is this related to any changes in the levels of markers in blood samples?

**6. OBJECTIVES AND OUTCOME MEASURES**

| Objectives                                                                                                                                           | Outcome Measures                                                                                                                                                                                                              | Timepoint(s) of evaluation of this outcome measure (if applicable)                                       |
|------------------------------------------------------------------------------------------------------------------------------------------------------|-------------------------------------------------------------------------------------------------------------------------------------------------------------------------------------------------------------------------------|----------------------------------------------------------------------------------------------------------|
| Primary objectives                                                                                                                            |                                                                                                                                                                                                                               |                                                                                                          |
| Assess the safety of hypofractionated radiotherapy to modify the stellate ganglia in patients with recurrent ventricular arrhythmia                  | Treatment related serious adverse events (SAEs) defined as any grade 3 toxicity requiring hospitalization or any grade 4 to 5 toxicity in the first 6 months as defined by the common terminology criteria for adverse events | During all hypofractionated radiotherapy sessions and monitoring visits up to 6 months post radiotherapy |
|                                                                                                                                                      | Treatment related side effects based on patient symptom questionnaires and clinical examination during study visits                                                                                                           | During all hypofractionated radiotherapy sessions and monitoring visits up to 6 months post radiotherapy |
| Secondary objectives                                                                                                                          |                                                                                                                                                                                                                               |                                                                                                          |
| Assess the feasibility of hypofractionated radiotherapy to modify the stellate ganglia to achieve anatomical and functional sympathetic denervation. | Physical modification of the stellate ganglia as assessed on MRI imaging                                                                                                                                                      | MRI scan at the final study visit 6 months post radiotherapy                                             |
|                                                                                                                                                      | Haemodynamic evidence of stellate ganglia modification determined by clinical and device-based heart rate dynamics and variability                                                                                            | Monitoring visits up to 6 months post radiotherapy                                                       |
|                                                                                                                                                      | Changes in circulating biomarker levels                                                                                                                                                                                       | Monitoring visits up to 6 months post radiotherapy                                                       |
|                                                                                                                                                      | The number of ventricular arrhythmias requiring device therapy                                                                                                                                                                | Monitoring visits up to 6 months post radiotherapy                                                       |
|                                                                                                                                                      | Patient reported outcomes about quality of life and symptoms based on KCCQ questionnaire                                                                                                                                      | Monitoring visits up to 6 months post radiotherapy                                                       |

|                                                                                                                                                                      |                                                                                                                                                                                          |                                                                             |
|----------------------------------------------------------------------------------------------------------------------------------------------------------------------|------------------------------------------------------------------------------------------------------------------------------------------------------------------------------------------|-----------------------------------------------------------------------------|
| Correlate the change in circulating biomarker levels with the efficacy of hypofractionated radiotherapy to modify the stellate ganglia in terms of arrhythmic burden | Changes in serum biomarker levels prior to compared to following intervention. Reduction in the number of ICD shocks/ATP in the 6 months before compared to the 6 months after treatment | During initial visit and monitoring visits up to 6 months post radiotherapy |
|----------------------------------------------------------------------------------------------------------------------------------------------------------------------|------------------------------------------------------------------------------------------------------------------------------------------------------------------------------------------|-----------------------------------------------------------------------------|

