A dose escalation protocol will be used to determine the lowest radiotherapy dose that can safely achieve sympathetic downregulation. This protocol will involve 13 patients with the doses escalated as follows: The first 3 patients would be treated at 8 Gy per fraction for 3 fractions on alternate days. If no serious adverse events occur then we will increase the dose to 9 Gy per fraction for 3 fractions on alternate days in the next 3 patients, 10 Gy per fraction for the next 3 patients for 3 fractions on alternate days and 11 Gy per fraction for 3 fractions on alternate days for the final 4 patients (figure 2). There will be a minimum of 6 weeks between the last participant treated at each dose before escalation the next dose to allow for detection of adverse events at participants' 6 week follow up visit. Before each dose escalation we will have an independent safety committee review all patient data and radiotherapy doses will only be escalated if there are no safety concerns.

Our study is a safety study, and we are powered to detect serious adverse events as our primary endpoint. Serious adverse events (SAEs) defined as any related and unexpected grade 3 toxicity requiring hospitalization, grade 4 toxicity or grade 5 toxicity as defined by the common terminology criteria for adverse events.

If a serious adverse event occurs, then no further fractions would be given to that patient and the dose would be reduced by 1 Gy for all subsequent patients (up to a total of 13 patients) without further dose escalation. If an SAE occurs at the lowest radiotherapy dose (8 Gy per fraction for 3 fractions) all subsequent patients will receive treatment at the even lower dose of 7 Gy per fraction for 3 fractions, if approved by our independent safety committee. However as highlighted in section 5 we have chosen a starting dose within the safe upper limit for neuronal tissue, so we do not anticipate this. An early stopping rule will be set to halt enrolment if 4 out of the first 8 patients develop and SAE. If patients withdraw from this trial then they will be replaced, and the study will continue until 13 patients have completed the dose escalation protocol (as detailed in section 9.8). We will not recruit any extra participants into our dose escalation protocol, unless participants withdraw, in which case they will be replaced. Once 13 participants complete the dose escalation protocol no further patients will be recruited.

Figure 2.

[figure not shown]

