Figure 2. The primary safety endpoints of this trial is any related and unexpected SAE occurring. SAE is defined in this trial as any Grade 5, Grade 4 or Grade 3 toxicity requiring hospitalisation as per the Common terminology criteria for adverse events (CTCAE v5.0). The first 3 patients will be treated at 8 Gy per fraction for 3 fractions on alternate days to achieve a total dose of 24 Gy. If no SAE is detected in any patient by 6 weeks, then the dose will be escalated by 1Gy per fraction for the subsequent 3 patients. This will be repeated up to a maximum dose of 11Gy per fractions (total 33Gy) for the final 4 patients. If any SAEs are detected then no further fractions of radiotherapy will be given to that patient, and the dose would be reduced

by 1Gy per fraction for all subsequent patients without further dose escalation during the trial. An early stopping rule will be set to halt protocol enrolment if  $\geq 4$  of the first 8 patients developed an SAE.

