#### **9.4. Description of study intervention(s), comparators and study procedures (clinical)**

##### **9.4.1. Description of study intervention(s)**

##### **Radiotherapy**

Modern radiotherapy is inherently delivered under image guidance. For this study we will have access to both CT and MRI based image guidance radiotherapy platforms, with comparable delivery accuracy on either platform. Oxford University Hospitals NHS Foundation Trust has an established on-site CT based radiotherapy service as well as access to MR-Linac based radiotherapy through service level agreements with GenesisCare.

CT based radiotherapy at the Oxford University Hospitals NHS Foundation Trust is delivered on a Varian TrueBeam™ system which combines cone beam computed tomography (CBCT) with a linear accelerator to deliver highly accurate radiotherapy. MR- based radiotherapy at GenesisCare is delivered on the MR-Linac platform. This combines 0.35T MRI imaging with a linear accelerator to again provide highly accurate radiotherapy. ...

For patients treated on the Varian TrueBeam, a conebeam CT scan will be taken prior to each radiotherapy treatment to ensure the patient is appropriately aligned to deliver treatment accurately. The

additional ionising radiation dose delivered during these scans is negligible compared to the ionising radiation dose delivered with each radiotherapy treatment.

The total radiation dose to the stellate ganglia is 24-33 Gy over the course of 3 fractions of treatment on alternate days. This radiation dose is targeted bilaterally to the lower half of the stellate ganglia and T1-2 paravertebral chain, with a rapid drop of to lower radiation isodose levels over adjacent dose sensitive structures such as the brachial plexus, spinal cord and trachea. Treatment will be planned while observing the organs at risk constraints i.e. acceptable limits of dose to the organ (57) and ensuring the dose to the ICD is within the threshold defined by the UK Royal College of Radiologists (63) and American Association of Physicists in Medicine (64).

Hypofractionated radiotherapy to the neck area is well tolerated (46, 65, 66) but may be associated with side effects related to the target and adjacent structures. Side effects from treatment of the stellate ganglion may result in side effects for cardiac sympathetic denervation, as listed below, including less commonly (<10%) hypotension, Horner's syndrome and upper limb and face hyperalgesia and hypohidrosis.

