### **10.3. Reporting Procedures for Serious Adverse Events**

A serious adverse event (SAE) occurring to a participant will be reported to the REC that gave a favourable opinion of the study where in the opinion of the Chief Investigator the event was 'related' (resulted from administration of any of the research procedures) and 'unexpected' in relation to those procedures. Reports of related and unexpected SAEs will be submitted within 15 working days of the Chief Investigator becoming aware of the event, using the HRA report of serious adverse event form (see HRA website).

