#### **11.2. Description of the Statistical Methods**

To measure our primary safety endpoint, we will measure the frequency of adverse events in the 6 months post radiotherapy. Our trial is powered to detect adverse event rates of 34% (see below)

For secondary outcome measures such as changes in circulating biomarker levels (NPY) and changes in number of device therapies following radiotherapy we will use non-parametric tests such as a Wilcoxon signed rank test to determine if changes are statistically significant.

To assess correlation between changes in biomarker levels and number of device therapies we will use a correlation matrix using non-parametric correlation tests such as Spearman rank-order correlation.

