#### **11.6. Stopping rules**

An early stopping rule will be set to halt protocol enrolment if  $\geq 4$  of the first 8 participants developed a related and unexpected SAE.

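### The primary safety event is defined inconsistently: treatment-related in the synopsis and section 6, related and unexpected in section 7, the Figure 2 legend and the halt rule in 11.6

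*Protocol*

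**What the plan says.** The synopsis and section 6 give the primary outcome as "Treatment related serious adverse events (SAEs) defined as any grade 3 toxicity requiring hospitalization or any grade 4 to 5 toxicity" within 6 months. The conditions are relatedness and grade. Expectedness is not mentioned.

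Section 7 names serious adverse events as the primary endpoint and says they are "defined as any related and unexpected grade 3 toxicity requiring hospitalization, grade 4 toxicity or grade 5 toxicity". The rule that lowers the dose by 1 Gy and ends escalation follows that definition and uses the same term.

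The Figure 2 legend opens with "The primary safety endpoints of this trial is any related and unexpected SAE occurring". Its next sentence defines an SAE by CTCAE v5.0 grade and hospitalisation alone, with neither relatedness nor expectedness. Its dose and halt sentences then say only SAE; the halt applies if at least 4 "of the first 8 patients developed an SAE". Section 11.6 gives the same halt as at least 4 "of the first 8 participants developed a related and unexpected SAE".

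Section 11.2 says: "To measure our primary safety endpoint, we will measure the frequency of adverse events in the 6 months post radiotherapy".

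Expectedness is explained in 10.3, where it decides what goes to the ethics committee: "Reports of related and unexpected SAEs will be submitted within 15 working days". It is the Chief Investigator's opinion, made in relation to the research procedures. Section 10.4 repeats the test for device complications. Section 9.4.1 lists foreseeable harms, "including less commonly (<10%) hypotension", Horner's syndrome and hyperalgesia among them, and long-term risks that include tracheo-oesophageal fistula, oesophageal narrowing and brachial plexus injury. No text says whether a listed harm of severe grade still counts.

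**The concern.** Expectedness is a reporting filter. It separates what an ethics committee needs to hear promptly from what it has already been told to anticipate. In the endpoint of a dose-escalation safety study it does something else: it can remove the toxicities the investigators foresaw, which are those escalation most needs to catch. Section 5 itself says that doses above 24 Gy in 3 fractions may reduce neuronal function, and the plan escalates to 33 Gy.

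Three things depend on the definition: the primary rate to be compared with 34%, the automatic dose reduction, and the 4-of-8 halt. Two analysts following different sections could report different rates from the same 13 patients. Investigators could also disagree on whether an event ends escalation. The definition is not deferred elsewhere, since 11.1 says no separate analysis plan is in use.

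**Working it through.** **Step 1. The texts side by side.** Take a treatment-related event of qualifying grade that is a listed risk, for example hypotension of grade 3 with admission, or a grade 4 brachial plexus injury.

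| Place | Conditions | Counted? |
|---|---|---|
| Synopsis, section 6 | related; grade | yes |
| Section 7 (endpoint and dose rule) | related; unexpected; grade | open to judgement |
| Figure 2 legend, endpoint sentence | related; unexpected | open to judgement |
| Figure 2 legend, SAE definition (its dose and halt sentences) | grade only | yes |
| 11.6 (halt) | related; unexpected | open to judgement |
| 9.6, Visits 4 to 6 (stop fractions) | serious; related | yes |

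The exclusion reaches the primary rate through section 7 and the Figure 2 endpoint sentence, the halt through 11.6, and the dose rule through section 7. Figure 2's own dose rule can be read without it.

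**Step 2. The plan's own figure.** Sections 11.3 and 11.7 state 13 patients for 80% power, one-sided alpha 0.05, to show a rate not exceeding 34% (range 9-34%). Reading this as 9% against 34%, the figure does not reproduce. The exact binomial test at n = 13 has power 0.671 and the smallest n with 80% power is 17; the usual normal approximation also gives 17. That is a separate matter. What follows uses only n = 13 and the 34% limit.

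**Step 3. How much one classification matters.** With X ~ Binomial(13, 0.34):

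- P(X = 0) = 0.66^13 = 0.0045
- P(X ≤ 1) = 0.0045 + 13 × 0.34 × 0.66^12 = 0.0347
- P(X ≤ 2) = 0.0347 + 78 × 0.34² × 0.66^11 = 0.1280

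At one-sided 0.05 the exact test passes with 0 or 1 event and fails with 2. The protocol names only a one-sample test for proportions. At 2/13 = 0.154, a z-test with the null variance gives z = (0.34 − 0.154)/√(0.34 × 0.66/13) = 1.42, p = 0.078, which fails. With the observed variance (Wald), z = 1.86, p = 0.031, which passes. The cut-off therefore depends on the test, but under any of them it lies at a very small count.

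**Step 4. Illustration only.** Let s be the share of related, qualifying events set aside as expected. The protocol gives no value, so s is assumed. The counted rate is p(1 − s).

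| s | P(≤1 of 13), p = 0.34 | P(≥4 of 8), p = 0.34 | P(0 of 3), p = 0.34 | P(≤1 of 13), p = 0.09 |
|---|---|---|---|---|
| 0 | 0.0347 | 0.2724 | 0.2875 | 0.6707 |
| 0.25 | 0.1187 | 0.1209 | 0.4135 | 0.7825 |
| 0.50 | 0.3249 | 0.0328 | 0.5718 | 0.8863 |
| 0.75 | 0.6957 | 0.0028 | 0.7661 | 0.9665 |

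At p = 0.09 the halt probability is 0.0034 with every event counted, so the wording hardly affects the halt there.

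**The case against.** The strongest reply is that patients are protected whichever wording applies. The committee reviews all data before each escalation and may recommend stopping. Any SAE under the wider 10.2 criteria found at follow-up pauses recruitment and treatment for review. Further fractions stop on any serious treatment-related event. Treatment-related side effects are a second primary outcome. All of this stands, and a reader should not infer that events would go unseen. But these safeguards are discretionary or apply to one patient; they do not say what enters the primary rate or the numeric rules.

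A reader might also infer that listed risks are definitely excluded, even at grade 4. The protocol does not support that. It has no formal list of expected events, and it describes the off-site neurological effects as generally mild and transient, so a severe instance could be judged unexpected. That argument is weaker for fistula and brachial plexus injury. What is established is that the count is left to opinion.

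Section 11.2 is thin support. With two primary outcomes, its wording may be loose shorthand for both rather than another definition.

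Two further inferences should be resisted. One is that the 34% comparison is unfair because of *unexpected*. That limit is an overall surgical complication rate, so setting it against severe events only is lopsided under section 6 as well, and deleting the word would not cure that. The other is that disabling events without admission should join the primary endpoint because 10.2 includes them. A broad review trigger beside a narrower dose trigger is legitimate, and adding a component would create a new endpoint rather than reconcile the existing one.

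**Conclusion.** The point holds as an inconsistency in the primary endpoint and the rules tied to it. Section 6 and the synopsis count every related event of the stated grades. Section 7 and the Figure 2 legend restrict the endpoint to unexpected events, and 11.6 restricts the halt. For the dose rule the restriction comes from section 7 alone, because Figure 2's SAE definition is by grade.

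The firm measure of size is that, under an exact test, the result turns between 1 and 2 events in 13 (p = 0.035 and 0.128), so one disputed classification could decide it. That rests on an exact test, which the protocol does not specify.

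The larger shifts in the table are not estimates. They need an assumed share of excluded events, and the rise from 3.5% to 70% also needs a 34% true rate of severe related events, whereas the protocol hypothesises fewer complications than surgery. At 9% the chance of passing moves from 67% to between 78% and 97%, and the halt is barely affected.

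**What to change.** Use one definition for the primary endpoint, the dose rule and the halt: treatment-related grade 3 toxicity requiring hospitalisation, or any treatment-related grade 4-5 toxicity (CTCAE v5.0), whether or not expected. Give it a label distinct from the 10.2 SAE, such as *primary safety event*, and use that label in the synopsis, sections 6 and 7, the Figure 2 legend, 11.2 and 11.6. Delete *unexpected* from section 7, Figure 2 and 11.6, and keep it only in 10.3 and 10.4. Leave 10.2 as the broader trigger for committee review in 10.1 and 13.3, and add no disability component.

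The cost is a wording amendment. Adverse events are already assessed at Visits 4 to 9, so no new data are needed. The counted rate may be slightly higher, which makes the 34% claim harder to meet, and a severe event of a listed kind would unambiguously lower the dose for later patients and end escalation.

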|                 | biomarker levels with the efficacy of radiotherapy to modify the stellate ganglia in terms of arrhythmic burden | intervention. Reduction in the number of ICD shocks/ATP in the 6 months before compared to the 6 months after treatment | 6 months post radiotherapy |
| Intervention(s) | Hypofractionated radiotherapy to the stellate ganglia                                                           |                                                                                                                         |                            |
| Comparator      | There is no control group                                                                                       |                                                                                                                         |                            |

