## 8. PARTICIPANT IDENTIFICATION

### 8.1. Study Participants

We aim to recruit thirteen adult participants with structural heart disease and impaired LV systolic function who have a primary or secondary prevention MR-conditional ICD device and have received more than one appropriate shock or ATP therapy in the preceding 6 months. We will recruit patients who receive care from cardiology services of the Oxford University Hospitals NHS Foundation Trust. They should have had their ICD *in-situ* for a minimum of 6 months and should be on optimal guideline based medical therapy for heart failure at the time of enrolment. We would look to screen at least 16 patients to allow for a 20% drop out rate. Eligible patients will be invited to undergo a screening 1.5T MRI scan at OCMR to and to assess the feasibility of hypofractionated radiotherapy to target the stellate ganglia (ability to clearly visualise the stellate ganglia, size of the stellate ganglia and their proximity of nearby organs at risk, and ability to tolerate MRI scanning) and to provide a baseline imaging from which to assess for physical modification to the stellate ganglia after 6 months. Once confirmed that the patient would be suitable for hypofractionated radiotherapy treatment, they would have an appointment with our collaborating oncologists to have dedicated planning scans.

We implant over 150 ICDs per year at Oxford University Hospitals NHS Foundation Trust and currently have over 500 ICD patients set up on remote monitoring. We also perform between 50 and 75 VT ablations per year in this population most of whom would be eligible for recruitment. Identifying 13 patients with appropriate therapies via remote monitoring, device clinics and acute admissions (as a tertiary centre) should therefore easily be achieved over a 24-month period.

Heart failure participants are likely to be taking multiple medication including (but not limited to) ACE inhibitors, combined angiotensin receptor/neprilysin inhibitors, beta blockers, SGLT2 inhibitors and aldosterone antagonists, however none of the items in the study protocol will impact upon routine heart failure medications.

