### 8.2. Inclusion Criteria

#### General Inclusion Criteria

- Participant is willing and able to give informed consent for participation in the study.
- Male or Female, aged at least 18 years old.
- Known diagnosis of structural heart disease defined as any patient with impaired left ventricular ejection fraction (less than 55%) due to any cause including ischaemic cardiomyopathy, dilated cardiomyopathy, hypertrophic cardiomyopathy or Arrhythmogenic cardiomyopathy.
- CMR compatible ICD device implanted a minimum of 6 months ago, under follow-up at Oxford University Hospitals NHS Foundation Trust.
- Experienced more than one appropriate ICD therapy (shocks or ATP) for ventricular arrhythmia in the last 6 months
- Established on optimal guideline based medical therapy for heart failure and arrhythmia

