#### **11.3. Sample Size Determination**

Considering that all patients will have failed pharmacological treatments to prevent VT, the population is expected to be at particularly high risk and SAE rates  $\leq 34\%$  (as reported for surgical CSD), and efficacy rates of 50% would be clinically acceptable. To be 80% powered to demonstrate a SAE rate not

exceeding 34% (range 9-34%) on a one sided, one sample test for proportions (alpha 0.05) would require 13 patients. Considering that all patients will have failed pharmacological treatments to prevent dangerous heart rhythms, the population is expected to be at particularly high risk of further dangerous heart rhythms. Efficacy rates of 50% would be clinically acceptable. We anticipate screening at least 16 patients to allow for a 20% drop out rate, **which has been costed in our BHF grant.**

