#### **11.7. The Level of Statistical Significance**

We are 80% powered to demonstrate a SAE rate not exceeding 34% (range 9-34%) on a one sided, one sample test for proportions (alpha 0.05).

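### The 'before' count of ICD therapies largely overlaps the window that qualified the patient, so the planned significance test is biased toward a reduction, by an amount the protocol's figures cannot fix

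*Protocol*

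**What the plan says.** Four parts of the Protocol bear on this point.

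- **Entry.** Section 8.2 requires that the patient has "Experienced more than one appropriate ICD therapy (shocks or ATP) for ventricular arrhythmia in the last 6 months". Section 8.1 says the same: participants must "have received more than one appropriate shock or ATP therapy in the preceding 6 months".
- **Outcome.** Section 6, like the Synopsis, defines the arrhythmia-burden measure as "Reduction in the number of ICD shocks/ATP in the 6 months before compared to the 6 months after treatment".
- **Test.** For secondary outcomes, Section 11.2 names NPY and "changes in number of device therapies following radiotherapy we will use non-parametric tests such as a Wilcoxon signed rank test", in order to decide whether the change is statistically significant.
- **Comparator.** The Synopsis states "There is no control group".

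Section 11.1 says that no separate statistical analysis plan is in use, so Section 11.2 is the operative text. The Protocol has no run-in, no baseline period kept apart from the qualifying period, and no mention of regression to the mean.

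**The concern.** The entry rule puts a floor of two events on a 6-month count, and nearly the same 6 months then serve as baseline. No floor applies after treatment. Some patients qualify because their underlying rate is high. Others qualify because they had a bad half-year, and their next half-year will on average be quieter whatever is done. The mean count is therefore expected to fall with an inert treatment. The signed rank test takes no change as its null hypothesis, which is false here even without a treatment effect, and no control arm shows how large the spontaneous fall would have been.

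One of the research questions in Section 5 is whether the treatment reduces abnormal heart rhythms. A significant fall in therapies would be read as answering it. This is the only listed outcome that measures arrhythmia burden.

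**Working it through.** The Protocol gives no effect size, power or event rate for this comparison, so it has no figure to reproduce. The check asks how often the stated test would find a reduction when there is none.

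**Inputs from the Protocol.** Entry needs at least 2 therapies in 6 months (8.1, 8.2). The windows are 6 months before and 6 months after treatment (Section 6). N = 13 (Synopsis). The test is a Wilcoxon signed rank test (11.2).

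**Assumptions.**
- Each patient's count is Poisson, with a rate drawn from a gamma distribution of mean *m* per 6 months and shape *k*. Here *m* is the mean in the pool before the entry rule is applied.
- The treatment has no effect.
- The test is two-sided at 0.05. The only level the Protocol states, "one sided, one sample test for proportions (alpha 0.05", belongs to the SAE rate. The nominal chance of a significant *reduction* is therefore about 2.5%.

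**Expected fall when the two windows coincide.** With P0 = (k/(k+m))^k and P1 = P0·k·m/(k+m):

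- mean before, given entry: B = (m − P1)/(1 − P0 − P1)
- mean after, given entry: A = (k + B)·m/(k + m)

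For m = 2, k = 1: P0 = 1/3 and P1 = 2/9, so B = (2 − 2/9)/(4/9) = 4.00 and A = (1 + 4)·2/3 = 3.33. The fall is 17% with no treatment effect.

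For m = 10, k = 1: P0 = 1/11 and P1 = 10/121, so B = (10 − 10/121)/(100/121) = 12.00 and A = 13·10/11 = 11.82. The fall is 1.5%.

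**Simulated trials of 13, no effect: share with a significant reduction.** The gap is the time from eligibility to treatment. Where two values are given, two separate simulations differed slightly; a dash means that the setting was not run.

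| m, k | B → A (fall) | no gap | 1 month | 2 months | 3 months |
|---|---|---|---|---|---|
| 0.5, 0.3 | 3.13 → 2.14 (31%) | 45% | 34% | 22% | – |
| 1, 0.5 | 3.51 → 2.67 (24%) | 29% | 21-23% | 16% | 11% |
| 2, 1 | 4.00 → 3.33 (17%) | 18-19% | 12-14% | 10% | 6% |
| 4, 1 | 6.00 → 5.60 (7%) | 7% | 6% | – | 5% |
| 10, 1 | 12.00 → 11.82 (1.5%) | 3-4% | 4% | – | 3% |

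With a 6-month baseline independent of the qualifying window, the same patients show a fall of about 0%, and a significant reduction in 1.6-3.0% of trials. The excess therefore comes from selection on the baseline count, not from the test.

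**Sensitivity to the model.** The 45% is not a ceiling: with m = 0.5 and k = 0.5 the figure is about 62% with no gap. Variation within a patient from one period to the next also raises it. For m = 4, k = 1 it goes from 7% to 19% when that variation is added (gamma, shape 1).

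**The case against.** Several points on the other side are fair.

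- **The windows are not identical.** Qualification ends at enrolment and baseline ends at treatment. The radiotherapy consultation and planning scans fall between, and possibly the 6-week hold between dose levels. The table shows that this gap matters: at m = 2, k = 1 the rate drops from 18-19% to 6% over 3 months. It weakens the point without removing it at low rates.
- **Rates may be high and persistent.** The population has recurrent arrhythmia and is drawn partly from VT-ablation patients. At a mean of 10 per 6 months the excess over nominal is slight.
- **The study is a small proof-of-concept safety series.** This outcome is secondary, and nothing here touches the SAE endpoint.

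Three stronger readings are tempting, and the documents do not support them.

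- **That this is the trial's only efficacy signal.** Section 6 also lists MRI change in the ganglia, heart-rate dynamics, circulating biomarkers and KCCQ. None of these is defined by the entry count.
- **That the biomarker correlation is biased toward benefit.** A fall common to all patients leaves Spearman ranks unchanged, and regression unrelated to NPY would weaken a correlation. A spurious one would need NPY to follow the same transient peak, and nothing here shows that.
- **That the remark in Section 11.3, "efficacy rates of 50% would be clinically acceptable", could be met by regression to the mean.** The Protocol does not say 50% of what. Across gamma-Poisson settings with means of 0.5-4, 26-54% of patients at least halve their count with the qualifying baseline. With a clean baseline 20-37% still do so by chance, so most of that figure is ordinary Poisson variation.

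**Conclusion.** The point holds in a limited form. The baseline count is largely conditioned on the entry rule and there is no comparator, so a test of zero change can call an inert treatment beneficial more often than its nominal level. The direction of the bias follows from the Protocol's own text.

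The size does not, because it depends on event rates, dispersion and a gap that the Protocol does not give. Under the gamma-Poisson assumptions it runs from roughly nominal (3-4% at a mean of 10 per 6 months) to about 45% (mean 0.5, shape 0.3), against 2.5%. It can be higher in some low-rate settings. The conclusion is confined to the significance claim on therapy counts and does not extend to the primary safety endpoint. It is worth correcting because the correction is nearly free.

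**What to change.** In Sections 6 and 11.2:

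1. Report the before/after therapy comparison descriptively, as per-patient counts and rates per patient-month of observation. Attach no significance test and no claim of efficacy.
2. State that regression to the mean is expected because of the entry criterion.
3. Add a sensitivity analysis whose baseline rate comes from ICD-stored therapies outside the qualifying window: screening to fraction 1, plus history earlier than 6 months before screening where it exists. Present it as a rate ratio with an interval.

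**Cost.** The study team already accesses the remote-monitoring records (Section 9.6, ICD interrogation and monitoring), so the extra work is a little more extraction.

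**Limits.** Section 8.2 admits devices only 6 months old, so some patients will have no clean baseline beyond the gap itself, and precision for them will be low. In a worst-case check with a 1-month baseline for everyone and a Wilcoxon test on monthly rates, false benefit was about 1% but false harm 4-9%. Earlier history also assumes a stable underlying rate; worsening disease would bias it against the treatment. For these reasons the off-window baseline should be a sensitivity analysis and not the main one.
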